## Abstract

**Background:**

Postoperative cognitive dysfunction (POCD) is a serious and common complication after total knee arthroplasty (TKA) in the elderly. Studies have suggested that repetitive transcranial magnetic stimulation (rTMS) can reduce the levels of tumor necrosis factor-alpha (TNF-α), interleukin-1 beta (IL-1β), and interleukin-6 (IL-6) inflammatory factors in the hippocampus, inhibit neuroinflammatory responses in the brain, and reduce the damage to synapses, thereby improving cognitive dysfunction. However, the effectiveness of rTMS for POCD remains to be explored. Therefore, the aim of this study is to treat POCD after TKA in the elderly with rTMS to evaluate the clinical efficacy of rTMS for POCD.

**Methods:**

This single-center, randomized, sham-controlled, assessor-blinded, parallel-group trial will enroll 207 elderly patients undergoing TKA and allocate them 1:1:1 to control group, active rTMS group, or sham rTMS group. All participants will receive standardized perioperative management. In addition, patients randomized to the active rTMS group will undergo stimulation of the left dorsolateral prefrontal cortex (DLPFC) at 10 Hz, 2000 pulses per session (5 s trains with 25 s inter-train intervals; 100% resting motor threshold), once daily for five consecutive pre-operative days. The sham rTMS group will follow the identical target and schedule, but the coil will be oriented perpendicular to the skull to avoid effective cortical stimulation. Primary outcome includes incidence of POCD at postoperative day seven (MoCA-based item-level definition). Secondary outcomes include changes in the MoCA total score and a prespecified cognitive subtest battery comprising the Digit Span Test (DST), Digit Symbol Substitution Test (DSST), Trail Making Test (TMT), and Delayed Story Recall (DSR), together with changes in serum inflammatory markers (IL-1β, IL-6, TNF-α, and HMGB1), assessed at preoperative day six, preoperative day one, postoperative day three, and postoperative day seven.

**Discussion:**

This trial will contribute to addressing the effectiveness of perioperative rTMS stimulation in elderly patients with TKA, and will initially clarify that perioperative rTMS preventive intervention can produce neuroprotective effects to reduce oxidative stress and inflammation, and to some extent block the possible pathway of POCD occurrence, thereby reducing the risk of POCD occurrence.

**Trial registration:**

ClinicalTrials.gov ChiCTR2400081372. Registered on 29 February 2024.

**Supplementary Information:**

The online version contains supplementary material available at 10.1186/s13063-025-09158-1.

## Administrative information

Note: the numbers in curly brackets in this protocol refer to SPIRIT checklist item numbers. The order of the items has been modified to group similar items (see http://www.equator-network.org/reporting-guidelines/spirit-2013-statement-defining-standard-protocol-items-for-clinical-trials/).

## Introduction

### Background and rationale {6a}

Osteoarthritis of the knee is a highly disabling chronic joint disease with a prevalence of approximately 50% in people over 60 years of age and more than 80% in people over 75 years of age [1]. End-stage osteoarthritis of the knee is accompanied by severe joint degeneration, which has a significant impact on the patient’s quality of life, leading to chronic pain, functional limitations, and disability. Total knee arthroplasty (TKA) is an effective and economical treatment for end-stage knee osteoarthritis [2]. Although TKA is the most effective treatment, it is also considered one of the most invasive and painful orthopedic surgeries, which predisposes elderly patients to a variety of postoperative complications [3, 4]. Among them, postoperative cognitive dysfunction (POCD) is a common postoperative central nervous system complication, which is mainly manifested as a decrease in learning ability, memory function, and information processing ability and speed, in addition to personality changes and a decrease in social activities, accompanied by central nervous system damage [5]. Furthermore, POCD may lead to an increase in postoperative complications, prolong patients’ hospital stays, increase the burden on families and society, and seriously affect patients’ postoperative quality of life [6]. Up to now, the treatment of POCD is based on preoperative cognitive training, pharmacological intervention, intraoperative management, and pain management, and there is no particular treatment for POCD [7]. Therefore, elderly TKA patients are facing a serious risk of POCD, and it is urgent to find appropriate interventions to reduce the incidence of POCD in elderly TKA patients.

In a previous study, preoperative probiotic supplementation was found to be effective in reducing POCD in elderly patients after TKA [8]. It suggested that perioperative prophylactic intervention in our perioperative period can block the possible pathway of POCD occurrence to a certain extent. It is suggested that perioperative prophylactic intervention may block the pathway of POCD occurrence to some extent. However, the exact pathogenic mechanism of POCD is still unclear. In recent years, some studies have suggested that the inflammatory response has a central role in the development of POCD [9]. Moreover, it has been shown that levels of interleukin-1 beta (IL-1β), interleukin-6 (IL-6), and tumor necrosis factor-alpha (TNF-α) are elevated in both the peripheral and central nervous system after surgery in patients with POCD, and the degree of elevation is highly correlated with the severity and duration of POCD [10]. Additionally, surgery could promote the release and activation of high-mobility group box 1 (HMGB1). The activated HMGB1 participates in the innate immune response by binding to receptors on circulating bone marrow-derived monocytes and increases the synthesis and release of proinflammatory cytokines into the circulation, destroying the blood–brain barrier [11]. Importantly, the level of HMGB1 in peripheral blood is strongly associated with the development of POCD [12]. On this mechanistic background, targeting prefrontal control networks to modulate inflammatory signaling represents a plausible preventive strategy.

Repetitive transcranial magnetic stimulation (rTMS) is a painless and non-invasive neuromodulation technique. It can not only regulate nerve excitability and cortical function, but also modulate the activity of individual neurons [13], and it has been widely used in the treatment of a wide range of neuropsychiatric disorders. Studies have shown that cytokines (such as IL-1β, IL-6, and TNF-α) play a significant role in the pathophysiology of cognitive dysfunction. Moreover, rTMS has shown potential in regulating cognitive function by targeting the neuroinflammatory pathways associated with postoperative cognitive dysfunction (POCD). Recent studies exploring the effects of rTMS on inflammatory markers (such as IL-6 and TNF-α) also support its potential in alleviating neuroinflammation [14–16]. We hypothesize that, compared with sham rTMS and standardized perioperative management, perioperative left DLPFC rTMS will improve early postoperative cognition and attenuate perioperative increases in inflammatory biomarkers (IL-1β, IL-6, TNF-α, HMGB1). Accordingly, we designed a randomized, sham-controlled trial to test whether perioperative rTMS can improve cognition and modulate inflammatory responses after TKA.

### Objectives {7}

To investigate the effect of perioperative rTMS on postoperative cognitive function in elderly patients undergoing TKA.To test the hypothesis that POCD is closely related to inflammatory responses (especially activation of inflammatory factors IL-1β, IL-6, TNF-a, and HMGB1), and to investigate the role of perioperative rTMS prophylactic interventions in reducing oxidative stress and inflammation, and lowering the levels of inflammatory factors in delaying POCD.

### Trial design {8}

This single-center, randomized, sham-controlled, assessor-blinded, three-arm parallel-group trial will allocate participants to (1) standardized perioperative management (control), (2) active rTMS, or (3) sham rTMS. Active rTMS will be compared with sham rTMS and with standardized perioperative management during the perioperative period in elderly patients undergoing TKA. All participants will receive a standardized perioperative pathway comprising pre-operative functional assessment and quadriceps-strengthening exercises; intra-operative combined spinal–epidural anesthesia with tourniquet use and tranexamic acid; and post-operative multimodal analgesia with early mobilization. The overall study flow is shown in Fig. 1. The SPIRIT schedule of enrollment, interventions, and assessments (including timing of the five preoperative rTMS/sham sessions and all outcome timepoints) is presented in Table 1. The detailed intervention and assessment flowchart is provided in Fig. 2.

**Fig. 1 Fig1:**
[figure not shown]
Flowchart of the research procedure

**Fig. 2 Fig2:**
[figure not shown]
Flowchart of intervention and assessment

**Table 1 Tab1:**
[figure not shown]
SPIRIT schedule of enrolment, interventions, and assessments

Standard Protocol Items: Recommendations for Interventional Trials (SPIRIT) figure of enrolment, interventions and assessments

*rTMS* Repetitive transcranial magnetic stimulation, *MoCA* Montreal Cognitive Assessment, *DST* Digit span test, *DSST* Digit symbol substitution test, *TMT* Trail making test, *DSR* Delayed story recall, *CAM-CR* Confusion assessment method-Chinese reversion, *IL-1β* Interleukin-1beta, *IL-6* Interleukin 6,
*TNF-a* Tumor necrosis factor-alpha; HMGB1, high-mobility group box 1

## Methods: participants, interventions, and outcomes

### Study setting {9}

Patients who are scheduled to undergo TKA patients will be recruited to the Shanghai Fourth People’s Hospital. Patients who meet the following criteria will be considered for inclusion in the study.

### Eligibility criteria {10}

#### Inclusion criteria

The inclusion criteria are as follows: (1) age ≥ 60 years, male or female; (2) needed to be performed TKA due to knee osteoarthritis; (3) American Society of Anesthesiologists grade I to II; (4) Preoperative Montreal Cognitive Assessment (MoCA) ≥ 26 points; (5) normal speech and hearing, able to co-operate with rehabilitation assessment and rehabilitation therapy.

#### Exclusion criteria

The exclusion criteria will be following: (1) drug allergy, severe cardiovascular disease, hepatic or renal dysfunction; (2) use of sedative-hypnotics or medications with anticholinergic effects that cannot be discontinued at least 4 weeks prior to baseline; (3) contraindications to rTMS (e.g., history of epilepsy, cochlear implant recipients, patients with metal implants in the head or pacemakers in the heart); (4) those who are participating in other clinical trials; (5) postoperative complications such as lung 34 infection, pulmonary embolism, or stroke; (6) personal or legal representatives unable or unwilling to give written informed consent.

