#### Withdrawal criteria 

The Withdrawal criteria will be the following: (1) those who failed to follow the trial protocol treatment; (2) those who do not wish to continue in the trial; (3) those whose condition has worsened after the start of the trial or who have had a serious adverse event that makes continuation of the trial inadvisable.

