#### Active rTMS group

The active rTMS group will be given active rTMS treatment based on standardized perioperative management. Active rTMS will be delivered using a magnetic stimulator (YRD-CCY-1, YIRUIDE Medical Equipment, Wuhan, China) with a figure-of-eight 70-mm coil positioned tangential to the scalp over the left dorsolateral prefrontal cortex (DLPFC; 10–20 system F3). Stimulation will be applied at 10 Hz in 5-s trains with 25-s inter-train intervals, 2000 pulses per session, at an intensity of 100% of the resting motor threshold (RMT). RMT will be defined as the lowest stimulator output that elicits motor-evoked potentials (MEPs) ≥ 50 μV in the relaxed right abductor pollicis brevis in ≥ 5 of 10 trials. Sessions will be delivered once daily for five consecutive pre-operative days. No post-operative rTMS will be delivered in this protocol; surgery is scheduled within 24–48 h after the final pre-operative session. Participants will be continuously monitored; if intolerable local discomfort occurs, stimulation will be stopped immediately and documented.

Rationale for stimulation site: The left dorsolateral prefrontal cortex (DLPFC) is a hub of executive-control and working-memory networks implicated in early postoperative cognition. Against the peri-operative neuroinflammatory background relevant to POCD (e.g., IL-1β, IL-6, TNF-α, HMGB1), prefrontal neuromodulation offers a biologically plausible route to support cognition and modulate inflammatory signaling. Accordingly, the left DLPFC (F3) was selected as the stimulation target.

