### Criteria for discontinuing or modifying allocated interventions {11b}

Participant-level criteria and actions: An rTMS/sham session will be interrupted or discontinued if any of the following occur during or immediately after stimulation: (1) intolerable scalp discomfort or pain despite repositioning; (2) vasovagal syncope or pre-syncope; (3) sustained hypertension (> 180/110 mmHg), tachycardia (> 130 bpm) or clinically significant arrhythmia; (4) new focal neurological symptoms/signs; (5) any seizure; (6) coil-related skin heating/burn; or (7) persistent severe headache not relieved by simple analgesia, or any other event judged clinically significant and related to the procedure by the investigator. The session will be stopped, clinical care provided, and the event documented and reported per the Harms procedures (see {22}). Resumption of stimulation at a reduced intensity and/or fewer trains may be considered after resolution of symptoms at the investigator’s discretion. Occurrence of a seizure or any unanticipated serious adverse device effect will lead to permanent discontinuation of rTMS for that participant. Participants may also withdraw from the intervention at any time; unless consent is withdrawn, they will remain in outcome follow-up (intention-to-treat).

Trial-level pausing or termination: Decisions to pause, modify, or terminate the trial will be guided by the independent DSMB according to pre-specified safety triggers and overall safety review (see Interim analyses and stopping guidelines {21b} and Harms {22}). Illustrative triggers include: any definite device-related seizure; ≥ 2 rTMS-related SAEs or an rTMS-related SAE rate > 5% and exceeding the sham arm by ≥ 5 percentage points; any unanticipated serious adverse device effect; or a clear excess of all-cause SAEs in the active rTMS arm at a scheduled review. The DSMB will issue recommendations to the TSC and Sponsor/PI; final operational decisions will be made by the Sponsor/PI upon TSC advice.

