### Recruitment {15}

Recruitment will take place at Shanghai Fourth People’s Hospital during the elective TKA pathway. Potential participants will be pre-screened at the pre-assessment clinic and on the orthopedic ward against the eligibility criteria (e.g., radiographic severity consistent with Kellgren–Lawrence grade ≥ 3), with written informed consent obtained prior to allocation. Recruitment strategies include surgeon referral at pre-assessment clinics, ward-based screening, and patient-facing materials (posters and flyers). Accrual numbers will be reported only under Trial status; detailed inclusion/exclusion criteria are provided in the “Eligibility criteria {10}” section.

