### Methods in analysis to handle protocol non-adherence and any statistical methods to handle missing data {20c}

Analyses will follow the intention-to-treat principle, retaining all randomized participants in their allocated groups. To minimize loss to follow-up, we will employ proactive retention strategies (appointment reminders, flexible assessment windows, and phone/text follow-ups). For the primary endpoint and other repeated continuous outcomes, linear mixed-effects models will be estimated under a missing-at-random assumption using maximum likelihood; results will be stress-tested by prespecified sensitivity analyses including multiple imputation (*m* = 20) and a conservative worst-case scenario. Participants who deviate from the intervention protocol will remain in the ITT analysis; per-protocol/sensitivity analyses may be reported descriptively. We will not replace randomized participants; if attrition exceeds the prespecified allowance and materially threatens power, the TSC may, on DSMB advice and blinded aggregate information, approve extending recruitment to preserve target precision.

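### Exclusion criterion (5) can only be met after randomisation and so conflicts with the intention-to-treat rule, and the withdrawal criteria do not say that follow-up and analysis continue

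*Protocol article*

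**What the plan says.** Exclusion criterion (5) in the protocol article reads "postoperative complications such as lung 34 infection, pulmonary embolism, or stroke" (the stray number is a text artefact). The Withdrawal criteria name "those who failed to follow the trial protocol treatment" and, as item (3), "those whose condition has worsened after the start of the trial or who have had a serious adverse event"; item (3) ends with a qualifier about continuing in the trial being inadvisable.

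On timing, Recruitment {15} describes screening "with written informed consent obtained prior to allocation". The Active rTMS group section states "Sessions will be delivered once daily for five consecutive pre-operative days", with surgery 24–48 h after the last session. The sham arm has the same schedule. The primary time point in Outcomes {12} is postoperative day seven.

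On analysis, {20a} specifies intention-to-treat. Section {20c} does the same, "retaining all randomized participants in their allocated groups", and keeps patients who deviate from the intervention in that analysis. Section {11b} says of those who withdraw from the intervention without withdrawing consent that "they will remain in outcome follow-up (intention-to-treat" applies, and {18b} draws the same line between stopping the intervention and leaving follow-up.

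**The concern.** An eligibility criterion should rest on facts known when the patient is randomised. Criterion (5) rests on what happens after surgery. Staff who apply it as written would exclude a randomised patient with pneumonia, pulmonary embolism or stroke; staff who follow {20c} would keep that patient. Nothing in the article says which instruction prevails. The auditing section {23} has a supervisor check inclusion and exclusion criteria in a 25% sample, so such a patient could be recorded as an eligibility failure while {20c} requires that patient to be analysed.

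Patients with these complications are plausibly at higher risk of cognitive decline in the first week. If they leave before day seven, the primary outcome is never collected, and the missing-at-random methods in {20c} must then cover a loss that is probably related to the outcome. The Withdrawal criteria raise the same question less sharply: they speak of the trial rather than the intervention, and are silent on whether day-three and day-seven testing continues.

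**Working it through.** **Order of events.** Consent, then allocation ({15}); assessment on preoperative day six; five daily sessions in the active and sham arms; assessment on preoperative day one; surgery; assessments on postoperative days three and seven ({13}). A postoperative complication of the index operation falls after allocation and after the session course in every case.

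**The texts side by side.**
- Criterion (5) against {20a} and {20c}: the first excludes on a postoperative event; the others retain everyone randomised. Sections {11b} and {18b} do not help, because they concern stopping the intervention, not complications. No section reinterprets criterion (5).
- Withdrawal criterion (1), non-adherence, against {20c}: the first withdraws the patient; the second keeps deviators in the analysis. They are compatible only if withdrawal means withdrawal from the intervention, which the criterion does not say.
- Withdrawal criterion (3), worsening or a serious adverse event, against {11b}: the first concerns continuing in the trial; the second keeps patients in follow-up after they stop the intervention. Again the scope is unstated.

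**What removal could do.** The article gives no complication or withdrawal rates, so the removal figures below are assumptions. Take no true effect and a POCD risk of 0.40 in each arm ({14}). If a fraction c of an arm is removed and those removed have POCD risk q, the apparent risk is (0.40 − c·q)/(1 − c).
- q = 0.40: 0.40·(1 − c)/(1 − c) = 0.40 for any c. Removal unrelated to outcome does no harm.
- c = 0.05 in both arms, q = 0.70: 0.365/0.95 = 38.4% in each; risk ratio 1.00.
- c = 0.05 in the comparator and 0.10 in the active arm, q = 0.70: 38.4% against 0.330/0.90 = 36.7%; risk ratio 0.95, difference 1.8 points.
- The same fractions with q = 0.90: 0.355/0.95 = 37.4% against 0.310/0.90 = 34.4%; risk ratio 0.92, difference 2.9 points.
- With the arms exchanged, the last two ratios become 1/0.954 = 1.05 and 1/0.922 = 1.08, an apparent harm.

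**Worst case.** With 207/3 = 69 per arm and 28 POCD cases in each (28/69 = 40.6%), remove POCD cases only, from the active arm only:
- 3 removed: 25/66 = 37.9%, a gap of 2.7 points
- 5 removed: 23/64 = 35.9%, a gap of 4.6 points
- 7 removed: 21/62 = 33.9%, a gap of 6.7 points

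The planned difference in {14} is 15 points.

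**The case against.** The analysis rule is explicit and repeated: intention-to-treat in {20a} and {20c}, with deviators kept. No sentence says that data are deleted or that anyone is dropped from analysis, and eligibility is checked before allocation. On that view criterion (5) is a misplaced line with no effect. This stands in part: a reader might infer that the plan removes these patients from the primary analysis, and the document does not go that far. It does not rescue the criterion, which has no use at screening unless it means complications of earlier surgery, and nothing in the text limits it to those.

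The withdrawal criteria can be read with {11b}, {18b} and {20c} as ending the intervention only. That reading is workable, so it would be too strong to call them a flat contradiction; what is missing is the sentence that says so.

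A reader might also infer that removal is bound to be unequal because control patients have no sessions to miss. The document does not support that for the main contrast: active and sham have identical schedules, control patients also have protocol care to follow, and criterion (5) applies to all three arms. Unequal removal would need a difference in tolerance or complications, which is possible but not shown.

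Finally, {20c} plans multiple imputation and a worst-case sensitivity analysis, and {22} already records all adverse events. These can expose the effect of lost outcomes, but they cannot replace day-seven tests that were never done.

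**Conclusion.** Criterion (5) is wrong as written: it conditions eligibility on a post-randomisation event and cannot be applied together with the intention-to-treat rule. The withdrawal criteria are a weaker, secondary fault: their scope is unclear and needs one reconciling statement.

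The conclusion rests on the order of events and the wording, not on any assumed rate. The size of the harm is unknown. With no true effect, bias arises only if removal is both related to POCD and different between arms, and it can run either way. Under the assumed unequal removal (5% against 10%) the risk ratio moves to 0.95–0.92, or to 1.05–1.08 with the arms reversed. The 2.7 to 6.7 points are a one-arm worst case and should not be quoted as an expected bias. The correction is still warranted, because it decides who counts in the primary comparison and is cheap to make.

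**What to change.** Limit the eligibility criteria to facts known before randomisation by deleting criterion (5) for randomised participants. No safety information is lost: {22} already records all adverse events and names pneumonia as one of special interest.

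Reconcile the Withdrawal criteria with {11b}, {18b} and {20c}. State that non-adherence or stopping the intervention does not by itself end outcome follow-up, that every randomised patient is analysed in the allocated group, and that a day-seven outcome not collected for any reason is handled as missing data under {20c}. The clinical rules for stopping sessions, and the safety part of withdrawal criterion (3), remain for the sponsor to set; the change concerns only follow-up and analysis.

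The cost is amendment wording and possibly a few more day-three and day-seven assessments. The Trial status section describes enrolment as under way, so the change can still protect patients randomised after it.
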